# SPAR – a randomised, placebo-controlled phase II trial of simvastatin in addition to standard chemotherapy and radiation in preoperative treatment for rectal cancer: an AGITG clinical trial

**DOI:** 10.1186/s12885-019-6405-7

**Published:** 2019-12-17

**Keywords:** Rectal cancer, Chemoradiation, Statins, HMG-coA reductase inhibitor, Tumour regression grading

## Abstract

**Background:**

Retrospective studies show improved outcomes in colorectal cancer patients if taking statins, including overall survival, pathological response of rectal cancer to preoperative chemoradiotherapy (pCRT), and reduced acute and late toxicities of pelvic radiation. Major tumour regression following pCRT has strong prognostic significance and can be assessed in vivo using MRI-based tumour regression grading (mrTRG) or after surgery using pathological TRG (pathTRG).

**Methods:**

A double-blind phase 2 trial will randomise 222 patients planned to receive long-course fluoropyrimidine-based pCRT for rectal adenocarcinoma at 18+ sites in New Zealand and Australia. Patients will receive simvastatin 40 mg or placebo daily for 90 days starting 1 week prior to standard pCRT. Pelvic MRI 6 weeks after pCRT will assess mrTRG grading prior to surgery. The primary objective is rates of favourable (grades 1–2) mrTRG following pCRT with simvastatin compared to placebo, considering mrTRG in 4 ordered categories (1, 2, 3, 4–5). Secondary objectives include comparison of: rates of favourable pathTRG in resected tumours; incidence of toxicity; compliance with intended pCRT and trial medication; proportion of patients undergoing surgical resection; cancer outcomes and pathological scores for radiation colitis. Tertiary objectives include: association between mrTRG and pathTRG grouping; inter-observer agreement on mrTRG scoring and pathTRG scoring; studies of T-cell infiltrates in diagnostic biopsies and irradiated resected normal and malignant tissue; and the effect of simvastatin on markers of systemic inflammation (modified Glasgow prognostic score and the neutrophil-lymphocyte ratio). Trial recruitment commenced April 2018.

**Discussion:**

When completed this study will be able to observe meaningful differences in measurable tumour outcome parameters and/or toxicity from simvastatin. A positive result will require a larger RCT to confirm and validate the merit of statins in the preoperative management of rectal cancer. Such a finding could also lead to studies of statins in conjunction with chemoradiation in a range of other malignancies, as well as further exploration of possible mechanisms of action and interaction of statins with both radiation and chemotherapy. The translational substudies undertaken with this trial will provisionally explore some of these possible mechanisms, and the tissue and data can be made available for further investigations.

**Trial registration:**

ANZ Clinical Trials Register ACTRN12617001087347.

(www.anzctr.org.au, registered 26/7/2017)

**Protocol Version:** 1.1 (June 2017).

## Background

### Summary of clinical condition and current treatments

Colorectal cancer (CRC) is common: 3016 cases were diagnosed in New Zealand (NZ) in 2012 with 1283 deaths [1] and rectal cancer represents about one-third of all colorectal cancers in NZ [2]. In Australia, 5114 rectal cancer cases were diagnosed in 2011 with 2018 deaths in 2012 [3]. Rectal cancer usually presents with locally-advanced T3 disease that requires ‘short course’ radiotherapy (SCRT) or, more commonly, ‘long course’ preoperative chemoradiation (pCRT – in which either infusional 5-fluorouracil (5FU) or oral capecitabine are administered concurrently with radiotherapy) for 5–6 weeks before surgery, and often adjuvant post-operative chemotherapy. While these advances in the management of resectable rectal cancer have reduced local relapse to < 10% in most patients, those with higher tumour stage, or evidence on staging MRI scan of invasion of local nodes, mesorectal fascia or blood vessels, have substantially higher local relapse rates and poorer overall survival (OS) [4]. In addition, distant relapse still occurs in 25–30% of patients, with most dying within 5 years [5]. Adding more drugs (such as oxaliplatin or irinotecan) to pCRT increases toxicities but with no improvement in cancer outcomes [6]. Other strategies are being explored in phase 2 and 3 trials but none have yet changed the standard of pCRT (or, less commonly, SCRT).

Unfortunately, the majority of patients (about 60%) with high-risk tumours have poor responses of their tumour to pCRT, and this group have double the risk of relapse compared to good responders [7]. Furthermore about 10% of surviving patients suffer from long-term significant bowel toxicity from RT. [5, 8] There is a clear need for improved efficacy and reduced toxicity in the large number of rectal cancer patients treated with pCRT every year in NZ and Australia.

### Summary of findings from pertinent pre-clinical studies and clinical trials

Statins offer the opportunity to improve outcomes in the treatment of rectal cancer. A Danish population study of 295,925 cancer cases of all types revealed that the use of statins significantly improved overall survival (OS) and specifically in those with CRC (HR 0.79, 95% CI 0.74–0.85) [9]. Similarly, a registry study of 10,762 CRC patients from Taiwan reported that, on multivariate analysis, cancer-specific survival was independently and significantly improved in statin users (HR 0.72 *p* < 0.001) [10]. More recently a population-based cohort study of 7657 patients with CRC in the United Kingdom showed that statin use improved cancer-specific survival (HR, 0.71; 95% CI, 0.61–0.84) and all-cause mortality (HR, 0.75; 95% CI, 0.66–0.84) [11].

Preclinical studies have elaborated effects on cell signalling pathways that may contribute to better cancer outcomes with statins, many of which are independent of cholesterol metabolism [12]:
generation of pro-apoptotic, growth-inhibitory and pro-differentiation responses in tumours;inhibition of angiogenesis, invasion and metastasis;reducing inflammation and inhibiting radiation (RT)-induced gut and skin toxicities while radiosensitising tumour cells and maintaining tumour control compared to RT alone [13–20].

This correlates with retrospective clinical studies in which patients taking statins during RT or chemo-RT for rectal, bladder or prostate cancer had significantly higher rates of pathological complete response (CR), local control and progression-free survival, respectively [21–25]. The findings in three published retrospective studies using pCRT in rectal cancer patients were:
in 407 patients at the Cleveland Clinic, favourable pathological regression was seen in 65.7% of statin users vs. 48.7% of others, *p* = 0.004 (multivariate OR 2.25; 95% CI 1.33–3.82) [22].multivariate analysis of 891 Canadian patients from multiple centres showed a significantly higher pathological CR rate in statin users (OR 1.7, 95% CI 1.04–2.89, *p* = 0.044) [23];in 349 patients from Memorial Sloan-Kettering Cancer Center pathological CR was higher in statin users (30% vs. 17%), with multivariate OR 4.2 (95% CI 1.7–12.1; *p* = 0.003) [24].

Furthermore, in a prospective observational study of 308 patients treated with radical pelvic RT at the Royal Marsden Hospital, London, those taking statins had significantly reduced RT-induced bowel toxicity, both during treatment (*p* = 0.04) and 1 year later [26].

In contrast two smaller studies have not shown an apparent benefit. A retrospective New Zealand study of 129 rectal cancer patients showed neither reduced acute toxicity nor improved pathological CR rates in the 23% of patients who took statins during pCRT [27]. A US single-arm phase 2 trial recruited 53 prostate cancer patients to take lovastatin 20–80 mg daily for 1 year starting during external beam RT and/or brachytherapy to prevent late RT-induced rectal injury [28]. Persistent gastrointestinal symptoms at 2 years were seen in 32% of patients (grade 2 in 6%), which did not meet the primary endpoint. Furthermore no benefit from statins was seen in a meta-analysis of surgery for prostate cancer [25, 29], nor in a trial of adjuvant chemotherapy for colon cancer [30].

### Summary of the known and potential risks and benefits to human participants

The statin chosen for this trial, simvastatin (SIM), is a well-known and widely available HMG-CoA reductase inhibitor commonly used in the treatment of hypercholesterolaemia and ischaemic heart disease. In retrospective studies it reduces recurrence in breast cancer patients [31] and preclinical studies have demonstrated its beneficial interactions with RT. [32, 33] It is very well-tolerated in the majority of patients with < 2% of patients in clinical trials discontinuing simvastatin due to adverse events. The most common side effects include abdominal pain, diarrhoea, indigestion, and weakness. Rarer side effects include joint pain, memory loss, myalgia, and muscle cramps. In patients taking statins long-term there have been reports of hepatitis, rhabdomyolysis and myositis however these complications are rare (< 1% of patients). Serious allergic reactions to simvastatin are also rare. 40 mg daily is the highest dose well-tolerated [34].

### Rationale for trial endpoints

#### mrTRG and pathTRG

MRI-based tumour regression grading (mrTRG), a 5-point system validated by the MERCURY group [35], is used for the primary endpoint in this trial as it permits much more sensitive and reliable preoperative assessment of tumour regression following pCRT in rectal cancer patients than other methods used currently (endoscopy, CT, PET-CT, endoluminal ultrasound or routine MRI) [36, 37]. mrTRG has proven to be a good predictor of pathological tumour regression grading (pathTRG) after pCRT [38], as well as independently predicting DFS and OS [39]. In a separate study, mrTRG identified ten times as many pathological CR patients as clinical inspection of the tumour following pCRT, with no compromise of the false-positive rate [37].

The rate of favourable (grades 1–2) mrTRG is the primary endpoint for the SPAR trial, based on three recently-published pCRT rectal cancer trials [40, 41]. In the MERCURY-II trial [40] favourable (grades 1–2), intermediate (grade 3) and unfavourable mrTRG (grades 4–5) had 3-year DFS of 82, 72 and 61% respectively ([name], personal communication). The phase 2 EXPERT and EXPERT-C trials evaluated neoadjuvant chemotherapy followed by pCRT [41]. On pooled analysis of these trials, mrTRG performed 4 weeks after completion of pCRT was evaluable in 85.5% of 269 patients; favourable (mrTRG 1–2), intermediate (mrTRG 3) and unfavourable (mrTRG 4–5) outcomes were seen in 41.7, 30.9 and 27.4%, respectively. pathTRG was evaluable in 86.9% of 244 resected patients with favourable, intermediate and unfavourable scores seen in 35.4, 29.7 and 34.9% respectively. Favourable mrTRG was independently associated with PFS (HR 0.37, *p* < 0.001) and OS (HR 0.44, *p* = 0.006) [41].

While the mrTRG training provided in SPAR has been shown to achieve moderate-to-excellent agreement between expert and training radiologists [42], it is important to show independently in the SPAR trial that mrTRG can be successfully and reproducibly performed in multiple centres, and shows a strong correlation with pathTRG and clinically-important cancer outcomes.

While pathological CR with pCRT is associated with the best clinical outcomes, and is commonly considered the “gold standard”, the spectrum of response on standardised pathological tumour regression grading (pathTRG) systems correlates with DFS and overall survival (OS), and informs prognosis in the full spectrum of patients, not just the small minority with pathological CR. Thus a 4-tier system has been widely adopted, including in Australasia [43], but a 3-tier system derived from this (grouping the two most favourable grades) shows greater reproducibility (interobserver agreement κ = 0.84) and is recommended [44].

SPAR will provide independent validation of the correlation of mrTRG with pathTRG and cancer outcomes, as well as evaluating the reproducibility of mrTRG assessment by NZ and Australian radiologists (not yet commonly used) and pathTRG by pathologists (standard practice).

Early surrogates for tumour response to pCRT are being investigated in clinical trials, particularly for their potential to modify the extent of surgery, or possibly avoidance of surgery in those who achieve a radiological CR [36]. The importance of this is three-fold: firstly, mrTRG can assist surgeons in planning the extent of surgery based on the response to pCRT; for example, this could change whether a patient needs a permanent stoma or reduce the risk of positive circumferential resection margins. Secondly, some patients who appear to have clinical CR after pCRT are electing to avoid surgery, based on much less precise methods of assessing residual disease than mrTRG, so using mrTRG can improve the precision of assessment of likely pathological CR [36, 37]. Thirdly, the poor outcomes of patients with an unfavourable response to pCRT has led to proposals to use mrTRG to identify this group in clinical trials and evaluate if adding other treatment (such as different chemotherapy or biological therapy) prior to surgery can improve cancer outcomes (e.g. The TRIGGER Study; clinicaltrials.gov No. NCT02704520).

#### Timing of post-pCRT MRI

In the SPAR study, the second MRI is scheduled at 6–8 weeks after pCRT to allow for surgery at 7–12 weeks. Surgery is now commonly delayed to 10–12 weeks after completion of pCRT in anticipation of improved tumour regression with additional time after pCRT [45]. There are conflicting reports as to whether this is the case, based on pathological CR rates [46–48]. However, while the pathological changes in the tumour following pCRT are expected to evolve over many weeks, this may not improve DFS or PFS as these outcomes are most likely determined by the inherent tumour sensitivity to pCRT. This is supported by a retrospective Korean study of 1786 patients treated with pCRT for locally-advanced rectal cancer, in whom pathological CR rates were highest when surgery was performed 5–10 weeks after pCRT; those who had resection delayed to > 7 weeks after pCRT had significantly higher pathological CR rates but no difference in relapse-free or overall survival [49]. Of concern, a French prospective randomised controlled trial of surgery at 7 or 11 weeks after pCRT in 265 rectal cancer patients showed no significant difference in the primary endpoint of pathological CR rates but there was significantly higher post-operative morbidity and poorer quality of mesorectal excision in the 11 week group, possibly due to greater RT-induced fibrosis [47]. A retrospective US study in 6397 patients evaluating time between RT and resection for rectal cancer found that an interval > 60 days was significantly associated with inferior survival, lower rates of sphincter-preserving surgery and an increased rate of positive surgical margins [48]. This suggests that surgery could be optimally performed earlier than commonly practised currently, and SPAR will accommodate this range.

#### Translational endpoints

This trial is an important opportunity to identify whether assessment of systemic inflammation (reflected in the modified Glasgow prognostic score, mGPS) and the local inflammatory response (through characterising infiltrating lymphocytes) could be an important translational research component of a subsequent phase III trial of statins in rectal cancer patients. Additionally, it will allow us to evaluate the impact of SIM on the relationship between specific T-cell infiltrates in pre-pCRT biopsies and pathTRG in the resected tumours, and with normal tissue inflammation post-pCRT.

It is long-recognised that a local inflammatory response with infiltration of T-lymphocytes into CRC carries a better prognosis, independent of tumour stage [50, 51]. Conversely preoperative systemic inflammation, reflected in the blood neutrophil/lymphocyte ratio (NLR) or serum c-reactive protein (CRP) and albumin levels (summarised in the modified Glasgow Prognostic Score), correlates with worse prognosis, independent of stage and preoperative therapy [52]. This adverse prognostic relationship persists with elevated mGPS 3–6 months postoperatively [52]. While statins are anti-inflammatory [12] and reduce the NLR in patients with high cholesterol [53], it is not known whether they lower the NLR or mGPS in cancer patients.

The Immunoscore is a recently-validated test that characterises T-cell subsets infiltrating into the centre of the tumour and at the invasive margin of CRC by immunohistochemistry (IHC) for CD3 and CD8; higher scores correlate with a lower risk of relapse and improved DFS and OS, independently of stage [54, 55]. While the Immunoscore was validated in rectal cancer patients who had primary surgery, it cannot be applied to those patients who received pCRT because identification of central and margin regions is compromised due to tumour regression and fibrosis [56]. However, in diagnostic rectal biopsies taken prior to pCRT prominent infiltration of CD3+ and CD8+ T-cells strongly correlated with pathological CR rates following pCRT (56).

Statins have complex effects on T-cell biology, including induction of regulatory T-cells (Tregs), their migration into tumours and inhibition of the induction of Th1 and Th17 cells [57]. Tregs, which dampen immune responses, can differentiate into effector Tregs (eTregs); these display markers of both immune suppression and activation [58] and are associated with a positive patient outcome in CRC [59]. However, Treg populations in lymph nodes do not correlate with patient outcome, unlike their presence in the primary colorectal tumour [60].

### Overall purpose

The overall purpose of this trial is to determine the effect of SIM on outcomes of pCRT for rectal cancer. Outcomes will be evaluated both by tumour regression as well as the tolerability of pCRT, estimating the size of the benefit by MRI-based assessment as well as pathological assessment of tumour regression. In addition, we will examine the biological mechanisms involved. The study will also assess the reproducibility of assessing mrTRG and pathTRG by radiologists and pathologists in Australia and New Zealand. Furthermore, the information provided by the post-CRT mrTRG could influence the intended surgical plan and optimise timing of surgery depending on tumour response to pCRT.

A positive outcome, either improved tumour regression or reduced toxicity from pCRT or both, would lead to a larger phase III trial to confirm these findings. It may also lead to evaluation of statins in prospective trials in many other settings where radiation is used in cancer treatment. This trial is an important opportunity to identify whether the addition of SIM to pCRT significantly modulates systemic inflammation (reflected in the NLR and mGPS) and the local inflammatory response (through characterising infiltrating immune cells). If so, it would inform the inclusion of these translational research components in a subsequent phase III trial of statins in rectal cancer patients. It will also allow us to evaluate the impact of SIM on the correlation of T-cell infiltrates in pre-pCRT biopsies with pathTRG in the resected tumours, and with normal tissue inflammation after pCRT.

## Methods/design

SPAR is a randomised phase 2 study with the overall aim to evaluate the effect of SIM on efficacy and toxicity of pCRT in rectal cancer patients, and on systemic and local inflammatory responses. Recruitment of 222 patients is required to address the primary objective. The study will recruit patients from participating AGITG hospitals/institutions in Australia and New Zealand.

Primary Objective:

The primary objective is to compare rates of favourable (grades 1–2) mrTRG (by central review) following pCRT with SIM versus with placebo, considering mrTRG in 4 ordered categories: 1, 2, 3, 4–5 (proportion of patients with favourable mrTRG in SIM and placebo groups). mrTRG will be assessed by comparison of the MR scan taken after pCRT with the scan before pCRT, which will be performed using the MERCURY protocol (38), and images analysed as described [38].

Secondary Objectives:

Secondary objectives are to compare between the SIM and placebo groups treated with pCRT: 1) The rate of favourable (grades 1–2) pathTRG in resected tumours by central review (proportion of patients with favourable pathTRG at surgical resection); 2) The incidence of > grade 2 acute GI and non-GI adverse events, assessed using CTCAE version 4.03; 3) The incidence of late GI adverse events; 4) Compliance with intended pCRT (proportion of patients completing > 90% of planned pCRT without dose reductions or delays); 5) Compliance with trial medication (proportion of patients receiving > 90% of the planned trial medication); 6) The proportion of patients undergoing surgical resection post-pCRT; 7) 3-year local recurrence (LR) rate, disease-free survival (DFS) and cancer-specific survival (CSS) (3-year LR rate, DFS and CSS); 8) the pathological scores determined by the central pathologist for radiation colitis in irradiated rectum in the resected specimen (radiation colitis scores).

Translational Science Objectives:

A number of correlative/translational objectives are intended. We aim to determine in the total trial population: 1) The association between mrTRG and pathTRG grouping (association between mrTRG and pathTRG grouping); 2) The inter-observer agreement between site radiologists and a central radiologist on mrTRG scoring (inter-observer agreement on mrTRG scoring); 3) The inter-observer agreement between site pathologists and a central pathologist on pathTRG scoring (inter-observer agreement on pathTRG scoring). In addition we aim to compare between the SIM and placebo groups treated with pCRT: 1) The association between CD3+ and/or CD8+ T-cell infiltrates in the tumour in the pre-pCRT diagnostic biopsies and pathTRG (association between T cell infiltrates and pathTRG); 2) the intensity and distribution of subsets of infiltrating T-cells in irradiated normal and malignant tissue in the resected specimen; 3) The influence of SIM on systemic inflammation, assessed with the mGPS and the NLR (mGPS and NLR).

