### Statistical methodology

#### Sample size

The primary endpoint of this trial is rates of favourable mrTRG (grades 1 or 2). This will be analysed using ordinal regression with 4 ordered categories of mrTRG (1, 2, 3 and 4–5) to provide greater sensitivity. Based on published data using MRI 6–8 weeks after pCRT, the expected rate of mrTRG in the control group is 9% grade 1, 39% grade 2, 20% grade 3 and 32% grades 4–5. A 35% relative increase in favourable mrTRG would be a worthwhile difference to inform a phase III trial.

Based on an ordinal proportional odds assumption, a sample size of 222 patients (111 treated with SIM and 111 controls) will have > 80% power to detect a change in mrTRG rates to 17% grade 1, 48% grade 2, 16% grade 3 and 19% grades 4–5 with 95% confidence.

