#### Statistical analysis

Intention-to-treat analysis of results will be the primary analysis. In addition, an exploratory per protocol analysis will also be conducted which will exclude ineligible patients, those not taking trial medication when starting pCRT and those who withdraw their consent to participate prior to response evaluation.

The primary endpoint and all secondary endpoints expressed as proportions will be estimated, together with corresponding 95% confidence intervals based on exact binomial distributions. Kaplan-Meier curves will be calculated for all time-to-event endpoints. Rates at specific points in time (e.g. 3-year local recurrence rate) will be estimated from these Kaplan-Meier curves.

Inter-observer agreement is defined as the degree of agreement in mrTRG (or pathTRG) results when reviewed by the central radiologist (or pathologist) and the reporting site radiologists (or pathologists). Results for each of mrTRG and pathTRG will be reported separately in a 3X3 grid comparing favourable, intermediate, and unfavourable scores between central and site radiologists and pathologists respectively. Inter-observer agreement will be assessed using a weighted kappa statistic > 0.40 is defined as moderate agreement. This will be assessed for mrTRG after recruitment of 35 randomised patients to ensure procedural consistency and again at the conclusion of the trial.

Adverse events in each arm will be tabulated and graded according the NCI CTCAE version 4.03.

For analysis of translational objectives, association between CD3+ and CD8+ T-cell infiltrates in diagnostic rectal cancer biopsies and pathTRG following pCRT will be evaluated using the chi-square test for trend. The effect of SIM on subsets of T-cells in tumours and normal tissue will be evaluated by comparison of distribution of scores for each cell type in SIM and placebo groups using the chi-square test for trend. Changes in the NLR and mGPS over time will be analysed using repeated measures ANOVA.

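### pathTRG, the first-listed secondary endpoint, is compared only as a favourable proportion although three ordered tiers are recorded; a three-tier ordinal comparison would be a cheap, minor gain in efficiency

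*Protocol article*

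**What the plan says.** Under Methods/design, secondary objective 1 is "The rate of favourable (grades 1–2) pathTRG in resected tumours by central review (proportion of patients with favourable pathTRG at surgical resection". The primary objective in the same section adds that mrTRG is considered in four ordered categories; the pathTRG objective has no such clause.

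Statistical analysis provides that the primary endpoint and "all secondary endpoints expressed as proportions will be estimated, together with corresponding 95% confidence intervals based on exact binomial distributions". It names no between-arm model for pathTRG. The same section plans a 3×3 agreement grid for pathTRG using favourable, intermediate and unfavourable, so the three-tier grade will exist.

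For mrTRG, Sample size states: "This will be analysed using ordinal regression with 4 ordered categories of mrTRG (1, 2, 3 and 4–5) to provide greater sensitivity".

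The endpoint rationale (mrTRG and pathTRG) says that the pathTRG spectrum "informs prognosis in the full spectrum of patients, not just the small minority with pathological CR". It recommends a three-tier grouping, citing a kappa of 0.84.

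**The concern.** The trial's reason for treating mrTRG as ordinal applies equally to pathTRG, which is also an ordered regression scale. A favourable-or-not cut gives no credit to a patient who moves from unfavourable to intermediate. The article has no survival figures by pathTRG tier, but for the corresponding mrTRG groups it quotes 3-year DFS of 72% (intermediate) and 61% (unfavourable), so that boundary may matter.

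The article's Overall purpose section names both MRI-based and pathological assessment for estimating the size of the benefit. The pathological comparison will also rest on fewer patients, because not everyone is resected and not every specimen may be gradable. A less efficient analysis of that smaller sample makes it somewhat more likely that a real effect looks unsupported by pathology.

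**Working it through.** **1. Reproduce the plan's own figure (mrTRG).** Inputs from Sample size: "the expected rate of mrTRG in the control group is 9% grade 1, 39% grade 2, 20% grade 3 and 32% grades 4–5"; target 17/48/16/19%; "a sample size of 222 patients (111 treated with SIM and 111 controls"); 95% confidence, read here as two-sided 5%.

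The cumulative odds ratios implied by these rates are 2.07, 2.01 and 2.01. With Whitehead's proportional-odds formula,

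power = Φ( |log OR| × √[(N/12)(1 − Σ p̄ₖ³)] − 1.96 ),

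where p̄ₖ is the mean of the two arms' proportions in category k:

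- p̄ = 0.13, 0.435, 0.18, 0.255, so Σp̄³ = 0.107 and √[18.5 × 0.893] = 4.065.
- OR 2.03 (mean log OR): 0.708 × 4.065 − 1.96 = 0.917, power 82.0%.
- OR 2.00: 0.693 × 4.065 − 1.96 = 0.857, power 80.4%.

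The stated power above 80% reproduces. The same rates cut to favourable or not (48% v 65%, 111 per arm) give, by the usual two-proportion formula,

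Φ( [0.17 × √111 − 1.96 × √(2 × 0.565 × 0.435)] / √(0.48 × 0.52 + 0.65 × 0.35) ) = Φ(0.604) = 72.7%.

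So for mrTRG the ordinal analysis is worth about 9 points on the article's own figures.

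**2. Inputs for pathTRG.** The article gives no effect size, power or evaluable number for pathTRG, so these are assumptions:

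- Common odds ratio 1.8 to 2.2, carried over from the mrTRG assumption of about 2.
- Graded resections per arm: 111 at most. Applying the pooled-trial rates in the endpoint rationale, 222 × 244/269 × 0.869 = 175, about 87 per arm.
- Control split A: 35.4/29.7/34.9%, the only three-tier pathTRG distribution in the article. It comes from trials that gave neoadjuvant chemotherapy before pCRT.
- Control split B: 48.7% favourable, the rate in patients not taking statins in one retrospective pCRT series in the Background. Its grading may differ from SPAR's. The remainder is not given; 25.0/26.3% is assumed, with 20.0/31.3% and 30.0/21.3% as checks.

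**3. Worked case: split A, OR 2.0, N = 222.** Favourable odds 0.354/0.646 × 2 = 1.096, i.e. 52.3%. Odds for favourable or intermediate 0.651/0.349 × 2 = 3.731, i.e. 78.9%. The simvastatin split is therefore 52.3/26.6/21.1%.

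- Three-tier: Σp̄³ = 0.129; 0.693 × √[18.5 × 0.871] − 1.96 = 0.823, power 79.5%.
- Two-group (35.4% v 52.3%): power 72.1%.
- Loss: 7.4 points.

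**4. Range.** Power for three-tier v two-group, by formula and by simulation (tie-corrected Wilcoxon test, 200,000 replicates):

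| Control split | OR | Per arm | Formula | Loss | Simulation | Loss |
|---|---|---|---|---|---|---|
| A | 1.8 | 87 | 55.3 v 47.7 | 7.7 | 54.9 v 49.7 | 5.2 |
| A | 1.8 | 111 | 65.8 v 57.6 | 8.2 | 65.3 v 57.4 | 7.9 |
| A | 2.0 | 87 | 69.3 v 61.4 | 7.9 | 68.8 v 63.5 | 5.3 |
| A | 2.0 | 111 | 79.5 v 72.1 | 7.4 | 79.0 v 72.0 | 6.9 |
| A | 2.2 | 87 | 79.8 v 72.7 | 7.1 | 79.1 v 74.6 | 4.5 |
| A | 2.2 | 111 | 88.5 v 82.7 | 5.8 | 88.0 v 82.8 | 5.2 |
| B | 1.8 | 87 | 51.9 v 48.0 | 3.9 | 51.4 v 50.2 | 1.2 |
| B | 2.0 | 87 | 65.2 v 61.1 | 4.1 | 64.6 v 63.1 | 1.5 |
| B | 2.0 | 111 | 75.7 v 71.8 | 3.9 | 75.1 v 71.7 | 3.3 |
| B | 2.2 | 111 | 85.2 v 82.0 | 3.2 | 84.6 v 81.8 | 2.8 |

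Losses are taken before rounding. The two other divisions of split B's remainder also give losses between 1.0 and 4.0 points. Split A thus costs about 5 to 8 points and split B about 1 to 4.

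**The case against.** **Nothing stated is wrong.** Only the primary endpoint is sized, and pathTRG is one of eight secondary objectives in a phase II trial. That stands, and it limits this to an efficiency point.

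**The binomial sentence describes estimation.** It covers the primary endpoint too, which is nevertheless modelled ordinally, so it does not exclude an ordinal model for pathTRG. The full protocol or the SAP, neither of which is shown, could contain one. This stands in part: no binary test is stated. But the objective is worded as a single proportion, without the ordered-categories clause that mrTRG receives, and nothing shown provides for an ordinal comparison.

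**The favourable cut is a reasonable summary.** It follows the top boundary of the recommended three-tier system and matches the outcome in one of the cited retrospective series. That stands, and is why the proportion should be kept.

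**The effect is borrowed.** Nothing in the article supports a common odds ratio across pathTRG tiers, and the split that gives the larger loss comes from a different regimen. That stands and is the reason for giving a range.

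**Selection.** Excellent responders may be observed without surgery, which can thin out the top tier. That affects the two-group and the three-tier analysis alike, since both use resected patients only, so it does not favour either.

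**Conclusion.** The point holds as a minor, cheap improvement. The article fixes its first-listed secondary endpoint as a two-group proportion while holding three ordered tiers, and it gives no reason for treating pathTRG less sensitively than mrTRG. The cost is about 5 to 8 points of power under the 35.4/29.7/34.9% split, or about 1 to 4 points if the control favourable rate is near 48.7%. Both ranges assume a two-sided 5% level, a common odds ratio of 1.8 to 2.2 taken over from mrTRG, and 87 to 111 graded resections per arm.

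A reader might infer three stronger things that the article does not support:

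- That pathTRG is the trial's main confirmatory endpoint. It is an unpowered secondary one, and the Discussion leaves confirmation to a larger trial.
- That the loss is a settled 7 points. That figure lies in the upper part of a range resting on borrowed inputs.
- That a favourable proportion is an error. It is a legitimate summary that uses the data less efficiently.

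**What to change.** In secondary objective 1 and in Statistical analysis, state that pathTRG will be compared between arms by proportional-odds regression on favourable, intermediate and unfavourable, reporting the common odds ratio with its 95% confidence interval. Keep the favourable proportion in each arm, and the difference with its interval, as the summary. If the unseen SAP already does this, a cross-reference is enough.

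The cost is a sentence of wording; no new data, reader or procedure is needed. The one downside is reliance on the proportional-odds assumption, which the primary analysis already makes. Tabulating all three tiers by arm beside the retained proportion would show a marked departure from it. The change does not address the restriction to resected patients, which applies to either analysis.
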